**2 List of Abbreviations**

2.

|            |                                               |
|------------|-----------------------------------------------|
| BDI        | Beck Depression Inventory                     |
| BIA        | Bioelectrical Impedance Analyser              |
| CONSORT    | Consolidated Standards of Reporting Trials    |
| CSRI       | Client Service Receipt Inventory              |
| DXA        | Dual-energy x-ray absorptiometry              |
| EQ-5D      | EuroQol-5D                                    |
| HbA1c      | Glycosylated haemoglobin                      |
| HRQoL      | Health Related Quality of Life                |
| IPAQ       | International Physical Activity Questionnaire |
| IWQOL-Lite | Impact of weight on quality of life-lite      |
| 6MWT       | 6-Minute Walk Test                            |
| NHS        | National Health Service                       |
| PSS        | Personal social services                      |
| RYGB       | Roux-en-Y gastric bypass                      |
| SAP        | Statistical analysis plan                     |
| SG         | Sleeve gastrectomy                            |
| STS        | Sit-to-stand test                             |
| T2D        | Type 2 diabetes                               |
| WL         | Weight loss                                   |

### 3. 3 Introduction

The BARI-OPTIMISE trial is a Phase IV, double-blinded, randomised, placebo-controlled trial. The aim of this trial is to determine whether 24-weeks of subcutaneous liraglutide 3.0 mg causes greater percentage weight loss (%WL), reduction in adiposity, improvement in metabolic indices, physical function and health-related quality of life (HRQoL) than placebo in patients with suboptimal nutrient-stimulated glucagon-like peptide-1 (GLP-1) response and poor weight loss following gastric bypass or sleeve gastrectomy.

Minor revisions were made to SAP V3 to include analyses of missing outcome data using self-reported weights and analyses of % weight loss as a categorical variable as part of the supportive analyses, before database lock.

#### 1. 3.1 Purpose of the statistical analysis plan

This document contains details of the main quantitative, statistical, analyses for the BARI-OPTIMISE trial. These analyses will be pre-specified in order that they are not influenced by the collected trial data after unmasking. The statistical analysis plan (SAP) does not preclude the undertaking of further, ad-hoc, analyses, although the results of any such further analyses should be interpreted carefully. Furthermore, the SAP does not prevent the adaptation of any part of the trial analysis, should situations arise in which such adaptation is deemed necessary. The rationale for any such adaptation will be fully justified and transparent.

The SAP contains details of quantitative analyses only and does not describe any qualitative analyses.

#### 2. 3.2 Authorship

#### 3. 3.3 Organization of Data and Analyses

Following participant consent, screening and baseline measure collection, the randomisation procedure will be remotely carried out by the Sealed Envelope, an independent specialised company that provides 24/7 cover to undertake the randomisation and unblinding if required. The type of randomisation to be used is a stratified block randomisation with random block sizes. Subjects will be randomly assigned in a 1:1 ratio to receive either liraglutide 3.0 mg or placebo, stratified for type of surgical procedure and T2D status. This will be done by using either internet or telephone randomisation. Unmasking of randomisation group will occur once all data have been entered onto the trial database and checked, the database locked for analysis, the SAP has been finalized and approved and the primary analysis has been performed and the results replicated by another statistician. Stata

16 will be used for the analyses: the Stata programs and code to be used for statistical analyses will be prepared prior to the unmasking of data. Two statisticians will perform the analysis independently in relation to the primary outcome in order to ensure the accuracy of the results.

Prior to performing the main analyses, basic checks will be performed on the collected, masked, data to identify any anomalies. Each outcome (primary and secondary), key variables and baseline demographic variables will be checked for:

- missing values;
- values beyond an acceptable range;
- any other inconsistencies.

If missing values or other inconsistencies are present the corresponding data will be checked with the aid of the researchers and, where necessary, either corrected or deemed to be missing. Any such changes made to the dataset will be documented fully.

## **4. 4 Summary of Quantitative Trial Data**

### **4. 4.1 Observation times**

The times at which data are collected during the trial are as follows:

- Baseline (Week 0);
- Week 2;
- Week 4;
- Week 8;
- Week 17;
- Week 24.

### **4. 4.2 Summary of Outcome Measures**

#### **4. 4.2.1 Primary outcome**

The primary outcome of this trial is %WL from the baseline visit to the end of treatment visit at 24 weeks. Percentage weight loss will be calculated using the following formula: %WL = [(weight at the baseline visit–weight at the end of the 24-week treatment period)/ weight at the baseline visit] x 100, measured at the end of trial.

##### **4.2.1.1 Sample size**

Using the 20-week data from the SCALE trial [1], 66 patients (33 per group) will be needed to detect a difference of 5%WL using a two-sample t-test, assuming a common SD of 5.4% for the intervention (liraglutide + lifestyle) and control groups (placebo + lifestyle), 90% power, 5% statistical significance allowing for a 20% drop-out rate and rounding up. Stata 15 (using sampsi command) was used to perform the sample size calculation [2].

7. 4.2.2 Secondary outcome

The secondary outcomes of this trial are to compare changes in:

1. Fat (%), lean body mass (%) and bone density from baseline visit to end of 24-week treatment period, assessed using DXA scanning and a bioelectrical impedance analyser (BIA), between liraglutide 3.0 mg and placebo.
2. Circulating fasted glucose, insulin, HbA1c and leptin, and meal-stimulated glycaemic, gut hormone and appetite response from baseline visit to end of 24-week treatment period between liraglutide 3.0 mg and placebo.
3. HRQoL (aggregate scores) assessed using CSRI, EQ-5D and IWQOL-Lite from baseline visit to end of 24-week treatment period between liraglutide 3.0 mg and placebo.
4. Characteristics of attitude and symptom of depression (aggregate scores) assessed using BDI from baseline visit to end of 24-week treatment period between liraglutide 3.0 mg and placebo.
5. Physical fitness assessed using 6MWT (distance covered in m), STS test(s) and handgrip test (kg) from baseline visit to end of 24-week treatment period between liraglutide 3.0 mg and placebo.
6. Physical activity level assessed using IPAQ from baseline visit to end of 24-week treatment period between liraglutide 3.0mg and placebo.
7. Healthcare service usage from baseline visit to end of 24-week treatment period between liraglutide 3.0mg and placebo.

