## Visit 2: Baseline Assessment (Day 1)

All participants who have consented for the trial must meet all the inclusion and exclusion criteria as set out in section 6.1 and 6.2. No eligibility waivers or deviations will be permitted. Prior to the scheduled assessment, the investigator will contact the participants to follow a standard diet for the 24 hours prior to the visit day and to avoid alcohol and strenuous exercise. They will fast from 20:00 on the night before the study visit and drink only water. The investigator will also remind participants to complete and bring to the visit the food diary that would have been sent to them (electronically and/or via post) in advance and in preparation for the baseline data collection. The following baseline assessments will be carried out:

- Sociodemographic data.
- Physical examination.
- Vital signs (HR and BP).
- Urine pregnancy test for women of childbearing potential.
- Weight.
- BIA.
- Dual-energy x-ray absorptiometry (DXA) scanning.
- Blood tests:
  - ✓ Haematology: full blood count.
  - ✓ Serum biochemistry: renal, liver and thyroid function, glucose, lipids, HbA1c.
  - ✓ Gut hormone and adipokines.
- Physical function assessments:
  - ✓ 6 minute walk-test (6MWT)
  - ✓ sit-to-stand (STS) test
  - ✓ Hand-grip test

- 
- Physical activity levels using the International Physical Activity Questionnaire (IPAQ).
  - HRQoL questionnaires:
    - ✓ Impact of weight on quality of life-lite (IWQOL-Lite)
    - ✓ Beck depression inventory (BDI).
  - Health Economics questionnaires:
    - ✓ Adapted Client Service Receipt Inventory (CSRI) [26]
    - ✓ EuroQol-5D (EQ-5D) [27, 28]
  - Meal test: fasted baseline bloods and subjective appetite (assessed using validated visual analogue scores) will be undertaken. At t0 a 500 kcal liquid meal will be consumed within 10 minutes. Repeated blood sampling and appetite assessments will be undertaken (T15, T30, T60, T90, T120, T150 and T180). Glucose, gut hormones and adipokines will be monitored using our established protocols [25].
  - Counselling on lifestyle modification (500-kcal deficient diet and 150 minute of physical activity/week).
  - Collection of food diary (3 days of food intake: 2 weekdays, 1 weekend day) completed at home by participants.
  - Distribution of:
    - ✓ New food diary (3 days of food intake: 2 weekdays, 1 weekend day)
    - ✓ Drug diary

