### Subsequent assessments

#### Visits 3-6: Intervention Phase (Days 15, 29, 57 & 113) (+/- 3 days)

The following will be assessed at each of the trial visits:

Targeted physical examination.

- Vital signs (HR and BP).
- Weight.
- BIA.
- Concomitant medications.
- Drug diary review.
- Adverse event (AE) review.
- Review of glucose monitoring at home.
- Urine pregnancy test for women of childbearing potential.
- Collection of food diary and distribution of new one.

- 
- 389 • Counselling on lifestyle modification.
  - 390 • Review of:
  - 391     ✓ Drug diary
  - 392 • Injection training will be repeated at Visit 3 (day-15), as needed.

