### Secondary Outcomes

The secondary outcomes of this trial are:

1. To compare changes in fat (%), lean body mass (%) and bone density from baseline visit to end of 24-week treatment period, assessed using DXA scanning, between liraglutide 3.0 mg and placebo.
2. To compare changes in circulating fasted glucose, insulin, HbA1c and leptin, and meal-stimulated glycaemic index, gut hormones and appetite response from baseline visit to end of 24-week treatment period between liraglutide 3.0 mg and placebo.
3. To compare changes in HRQoL (aggregate scores) assessed using IWQOL-Lite and BDI from baseline visit to end of 24-week treatment period between liraglutide 3.0 mg and placebo.
4. To compare changes in characteristics of attitude and symptom of depression (aggregate scores) assessed using BDI from baseline visit to end of 24-week treatment period between liraglutide 3.0 mg and placebo.
5. To compare changes in physical fitness assessed using 6MWT (distance covered in m^2), STS test (s) and handgrip test (kg) from baseline visit to end of 24-week treatment period between liraglutide 3.0 mg and placebo.
6. To compare changes in physical activity level assessed using IPAQ from baseline visit to end of 24-week treatment period between liraglutide 3.0 mg and placebo.
7. To compare changes in healthcare service usage from baseline visit to end of 24-week treatment period between liraglutide 3.0 mg and placebo.

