#### 12. 5.4 Secondary analyses

##### Secondary outcomes

Exploratory analyses will be performed for secondary outcomes. Plots of %WL at Week 2, 4, 8, 17 and 24 will be presented for a random sample of patients to explore the effect of treatment over time. Analysis of repeated measurement for %WL will be performed using random effects linear regression model including intervention group, type of surgical treatment, diabetes status, baseline values of weight, time and an interaction of intervention effect and time in the model if appropriate. The %WL outcome will be categorised into 3 categories:  $\geq 5\%$ ,  $\geq 10\%$  and  $\geq 15\%$  and analysed using proportional odds model including intervention group, type of surgical treatment, diabetes status and baseline values of weight. If the model does not converge due to small numbers, a descriptive comparison will be carried out or a binary category will be used. Plots will also be used to show the trends of other continuous outcomes (e.g. fat, lean body mass, bone density, circulating fasted glucose, insulin, HbA1c and leptin, meal-stimulated glycaemic, gut hormone and appetite response) from baseline to the end of 24 weeks. These secondary continuous outcomes measured at

24 weeks will be analysed by fitting linear regression models, adjusting for type of surgical treatment, diabetes status and baseline values of the outcomes. Random effects models will be used to analyse repeated measures of the secondary outcomes. The normality assumption will be checked for each model. If violated, a suitable transformation/non-parametric method will be considered. All analyses will be carried out comparing the intervention and control groups as randomised using all available data (intention to treat analysis). Mean differences in each outcome will be reported with 95% confidence intervals.

Table 2. Secondary outcomes over time.

| Outcome                    | Units / Category | Baseline | Week 4 | Week 8 | Week17 | Week 24 |
|----------------------------|------------------|----------|--------|--------|--------|---------|
| %WL                        |                  |          |        |        |        |         |
| Fat                        |                  |          |        |        |        |         |
| Lean body mass             |                  |          |        |        |        |         |
| Bone density               |                  |          |        |        |        |         |

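### Lean body mass is specified only as a percentage, so a real loss of lean tissue can read as a gain; DXA fat and lean mass in kilograms should be added.

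*Combined protocol and SAP*

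**What the plan says.** The secondary objective (protocol, Secondary objectives, item 1; repeated in the SAP Study Summary) is change in fat, lean body mass and bone density, with no unit. Both outcome lists then fix the scale. Protocol, Secondary Outcomes, item 1 reads "To compare changes in fat (%), lean body mass (%) and bone density", and SAP 4.2.2, item 1 reads "Fat (%), lean body mass (%) and bone density from baseline visit to end of 24-week treatment period". Neither gives a kilogram version, and the units column of SAP Table 2 is blank.

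The two documents differ on the instrument. The protocol has "assessed using DXA scanning, between liraglutide 3.0 mg and placebo"; the SAP has "assessed using DXA scanning and a bioelectrical impedance analyser (BIA), between liraglutide 3.0 mg and placebo". In the protocol's visit lists, DXA appears at baseline (Visit 2) and end of treatment (Visit 7). BIA appears at both of those and at Visits 3-6.

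SAP 5.4 analyses week-24 secondary outcomes by linear regression adjusted for surgery type, diabetes status and the baseline value. It adds that "Random effects models will be used to analyse repeated measures of the secondary outcomes". Table 2 gives one row each to fat, lean body mass and bone density, with columns for baseline and weeks 4, 8, 17 and 24 and no device label. The protocol treats secondary results as exploratory.

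**The concern.** A percentage of body weight has a denominator that the treatment is meant to shrink. If liraglutide works and most of the lost weight is fat, lean tissue becomes a larger share of a smaller body even as its absolute amount falls. A reader who wants to know what happened to lean body mass would see a positive treatment difference in lean % when more lean kilograms had been lost on active drug. The adjusted regression does not correct this, because the reversal comes from the outcome scale and not from baseline imbalance.

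The instrument question is secondary. The SAP adds BIA to an outcome that the protocol assigns to DXA and does not say which device supplies the reported value.

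**Working it through.** **The plan's own figures.** The documents give no design figure for fat or lean mass. The only sample-size figure, 66 patients for the primary outcome, reproduces: a t-based calculation for a 5-point difference, SD 5.4 and 90% power gives 26 per arm; 26/0.8 = 32.5, rounded up to 33, or 66 in total. Nothing below changes it.

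**Formula.** Let W0 be baseline weight, L0 the baseline lean fraction, w the fractional weight loss and s the share of lost weight that is lean.
- Lean mass after treatment = W0(L0 − s·w); weight after treatment = W0(1 − w).
- Change in lean kg = −s·w·W0, which is negative whenever any lean tissue is lost.
- Change in lean fraction = (L0 − s·w)/(1 − w) − L0 = w(L0 − s)/(1 − w).

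So lean % rises if s < L0, is unchanged if s = L0, and falls if s > L0.

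**Within one arm.** Assumed inputs, none of them in the documents: W0 = 110 kg, L0 = 0.55, w = 0.07, bone ignored. Baseline lean mass is 60.5 kg, weight lost is 7.7 kg and final weight is 102.3 kg.

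| Lean share s | Lean mass after (kg) | Change (kg) | Lean % after | Change (points) |
|---|---|---|---|---|
| 0.15 | 59.3 | −1.2 | 58.0 | +3.0 |
| 0.25 | 58.6 | −1.9 | 57.3 | +2.3 |
| 0.35 | 57.8 | −2.7 | 56.5 | +1.5 |

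**Wider range.** At 110 kg, with L0 from 45% to 55% and weight loss from 5% to 10%:
- s = 0.25: lean mass falls 1.4 to 2.8 kg; lean % rises 1.1 to 3.3 points.
- s = 0.35: lean mass falls 1.9 to 3.9 kg; lean % rises 0.5 to 2.2 points.
- Boundary, at L0 = 0.55: with s = 0.55 lean % does not move; with s = 0.60 it falls by 0.3 points at 5% loss and 0.6 points at 10% loss.

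**Between arms.** Take the design difference of 5 percentage points as an assumed 7% versus 2% loss, with W0 = 110 kg, L0 = 0.55 and s = 0.25 in both arms.
- Lean kg lost: 0.25 × 7.7 = 1.925 versus 0.25 × 2.2 = 0.55, so liraglutide loses about 1.4 kg more.
- Lean % gained: 0.07 × 0.30/0.93 = 2.26 points versus 0.02 × 0.30/0.98 = 0.61 points, so liraglutide appears about 1.6 points better.

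With equal baselines, adjusting for baseline lean % leaves this difference as it is. With bone ignored, fat % is the complement of lean %, so it falls as fat mass falls and has no sign problem here.

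**Instruments against visits.** Visits 3-6 list BIA but neither DXA nor laboratory blood tests. So the week 4, 8 and 17 cells of Table 2 can hold only BIA values for fat and lean mass, and have no listed source for bone density, fasting glucose or insulin. Baseline and week 24 have both devices. If one row used DXA at the ends and BIA between, an assumed constant offset of 2 to 4 points would appear as a shift of that size at week 4 and a reverse shift at week 24, with no true change. An offset common to both arms cancels in the between-arm difference at any one visit.

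**The case against.** Several points on the other side are sound. The hypothesis speaks of adiposity, which fat % measures properly. No hypothesis of preserved or increased lean mass is stated, and a rise in a result labelled as a percentage is a true statement about composition. It misleads only when read as an amount of tissue. Weight is taken at the same visits, so kilograms can be derived. Every body-composition input above is assumed, and the reversal depends on the lean share staying below the baseline lean fraction. All of this stands. It narrows the point to lean %, but it does not remove it: the stated objective is change in lean body mass, and the only outcome specified for it can move in the opposite direction.

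A reader might also infer that the SAP merges DXA and BIA into one series. The documents do not say so. Naming two devices under one item fits separate reporting equally well. Both devices are used at baseline and week 24, so the defined change can be computed within either one. Table 2 looks like a generic shell: it has mid-trial columns for bone density, which has no listed source at those visits, and omits week 2, when weight and BIA are taken. The sentence on random-effects models naturally covers only outcomes that are measured repeatedly. What remains is missing detail.

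One route deserves closing. SAP 5.5 allows missing week-24 values of the primary outcome to be imputed from other time points, and allows the same strategy for secondary outcomes where appropriate. For fat and lean mass only BIA exists at the intermediate visits. If DXA values were filled from it and drop-out differed by arm, a device offset would no longer cancel.

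**Conclusion.** The concern holds for the scale of the lean-mass outcome. As specified, lean % can show an advantage for the arm that lost more lean tissue: about 1.6 points in its favour against about 1.4 kg more lost, in the worked contrast. The sign reverses whenever the lean share of lost weight is below the baseline lean fraction, and not otherwise. The sizes rest on assumed weight, composition, weight loss and lean share, since the documents give none of these for body composition.

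It would go too far to say that the sign is always wrong, that fat % is unsound, or that device differences contaminate the planned week-24 comparison. The instrument question is a clarification. It rests on the protocol's visit lists, because the schedule in Appendix 1 was not available for this review.

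The change should be made because this is a named objective and the remedy is nearly free. The outcomes are exploratory, and the primary analysis and sample size are unaffected.

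**What to change.** In SAP 4.2.2 and 5.4, add DXA fat mass (kg) and DXA lean mass (kg) at week 24, each analysed by the existing linear regression adjusted for its baseline value in kg, surgery type and T2D status. State that these results answer the body-composition objective, and report the prespecified percentages alongside.

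As clarifications:
- name DXA as the source for the week-24 comparison, in line with the protocol;
- present BIA as a separately labelled series, with any repeated-measures model for fat or lean mass fitted to BIA alone;
- state that missing DXA values are not imputed from BIA;
- fill in the units column of Table 2 and restrict each row to visits at which that measure is taken.

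The cost is SAP wording, a table edit and one or two extra result rows. The DXA scans are already scheduled at both visits, so no new measurement is needed.

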**5. 5 Analyses**

8. 5.1 Recruitment and Retention

A CONSORT diagram [3] (Page 9 as an example) will be presented to provide a detailed description of patient numbers at each time point during the trial. In addition, a table summarizing the numbers of drop-outs at each stage of the trial and reasons for drop-out (if given) will be presented.

Consort diagram

CONSORT 2010 Flow Diagram

6.1 Enrollment

Assessed for eligibility (n= )

Excluded (n= )  
♦ Not meeting inclusion criteria (n= )  
♦ Declined to participate (n= )  
♦ Other reasons (n= )

Approached (n= )

Pending Screening finalisation (n= )

Screened (n= )

Excluded (n= )  
♦ Not meeting inclusion criteria (n= )  
♦ Declined to participate (n= )  
♦ Other reasons (n= )

Randomized (n= )

3.1 Allocation

Allocated to intervention (n=)  
♦ Received allocated intervention (n=)  
♦ Did not receive allocated intervention (give reasons) (n= )

Allocated to intervention (n=)  
♦ Received allocated intervention (n=)  
♦ Did not receive allocated intervention (give reasons) (n= )

